### 5.4 Exclusion Criteria

Individuals meeting any of the following criteria will be excluded from participation in this study:

- Age  $< 18$  years or  $> 78$  years
- Smoking
- Triglyceride level  $> 400$  mg/dL
- More than 14 alcoholic drinks per week
- Chronic illness (e.g., diabetes, atherosclerosis, rheumatoid arthritis, ...)
- Acute inflammation
- Pregnancy or intention to become pregnant during the study period
- Breastfeeding
- Regular use of dietary supplements (see §6.8 Concomitant Therapy)
- Use of (chronic) medication (see §6.8 Concomitant Therapy)

## 5.5 Lifestyle Considerations

### 5.5.1 Meals and Dietary Restrictions

There are no meal or diet restrictions.

At the start and end of the study, participants will complete a food questionnaire indicating the frequency with which they consume certain foods. This is to map the dietary habits of the study population.

Participants are asked not to change their eating habits during the study to avoid any influence on the results.

### 5.5.2 Caffeine, Alcohol, Tobacco, and Other Habits

Participants may not smoke or consume more than 14 alcoholic drinks per week.

### 5.5.3 Physical Activity

No restrictions regarding physical activity are imposed.

Participants are asked not to change the amount of physical activity during the study to avoid any influence on the results.

## 5.6 Screen Failures

If a potential participant is not eligible for this study, they will not be randomised. The participant will be informed by phone or email.

The option to schedule a new screening visit is not included in the protocol.

## 5.7 Recruitment Methods

Eligible patients from collaborating physicians/group practices will be briefly introduced to the study by the physician involved. If interested and after explicit consent, the contact details of these patients will be passed on to the NatuRAPT researchers. After providing detailed information, they will handle the practical details regarding possible inclusion.

The study will also be presented to UAntwerp staff via the website/email/Pintra. A flyer may provide an initial brief explanation. In case of slow recruitment, outreach may be expanded to UZA staff, pharmacies, and other cardiologists/general practitioners. Press releases will also be distributed. Doctors and pharmacists may receive compensation for referring eligible participants. For each included participant, the doctor or pharmacist will receive €20, or €150 for every 5 included participants.

## 5.8 Compensation

Participants will receive a €20 book voucher upon completion of the study, meaning at the end of the final visit. If, after unblinding, the participant is found to have taken the placebo, they will receive one package of 112 capsules (for 8 weeks) free of charge.

## 6. Trial Intervention and Concomitant Therapy

### 6.1 Description of Trial Intervention

The study product is the standardised olive extract Tensiofytol® from the manufacturer Tilman. It contains a recommended daily amount of 334 mg olive leaf dry extract and 106 mg olive fruit dry extract (*Olea europaea* L.; equivalent to 100 mg oleuropein and 20 mg hydroxytyrosol), divided over 3 capsules.

During the study, 3 capsules must be taken orally each day with a glass of water at dinner for 8 weeks or until the evening before the final visit (maximum 9 weeks after starting intake). The participant will receive a container with 210 capsules, sufficient for 10 weeks of treatment. The packaging must be stored at room temperature (15–25 °C).

The packaging is labelled with the following label:

[figure not shown]

The placebo contains magnesium stearate, calcium phosphate, colloidal silica, microcrystalline cellulose, and talc.

During the study, 3 capsules must be taken orally each day with a glass of water at dinner, for 8 weeks or until the evening before the final visit (maximum 9 weeks after starting intake).

The participant will receive a container with 210 capsules, sufficient for 10 weeks of treatment.

The packaging must be stored at room temperature (15–25 °C).

The label and appearance are identical to those of the study product.

### 6.2 Rationale for Trial Intervention

The dose and administration correspond to the posology of the commercially available product Tensiofytol®.

For practical reasons, the same amount of product is divided over 3 capsules instead of 2 capsules as available in the public pharmacy.

### 6.3 Dosing and Administration

The participant must take 3 capsules orally at the same time. This should be done with the evening meal for 8 weeks or until the evening before the final visit (maximum 9 weeks after starting intake).

The study product should be taken while sitting upright and with a glass of water.

No dose adjustments are allowed.

## 6.4 Treatment of Overdose

In case of overdose, contact must be made with the principal investigator – medical monitor. They will assess the situation. If they are not reachable, the participant will be referred to emergency services. The UZA emergency department can be contacted at:  
[name]

## 6.5 Preparation, Handling, Storage and Accountability

### 6.5.1 Preparation of Trial Intervention

The study product and placebo are prepared by the manufacturer. The containers are shipped by mail to the NatuRAPT researchers.

The content of oleuropein and hydroxytyrosol is verified by NatuRAPT (see protocol “Quantification of Olive Polyphenols in Extract”).

### 6.5.2 Handling and Storage of Trial Intervention

The containers are shipped by mail and stored at room temperature (15–25 °C) by the NatuRAPT research group.

When distributed to participants, the product will be handed over physically or sent by mail.

The products remain stable for at least 3 years after preparation.

Stability is monitored by the manufacturer.

### 6.5.3 Accountability of Trial Intervention

The product is delivered to the participant by the NatuRAPT researchers. During the final visit, any remaining study product is returned to the researchers and stored by them.

Delivery and return of the study products are recorded in the “Drug Dispensation & Accountability Log.”

## 6.6 Participant Assignment, Randomisation and Blinding

### 6.6.1 Participant Assignment

Participants will be stratified by sex and randomised after collecting and reviewing the inclusion criteria.

### 6.6.2 Randomisation

Participant numbers will be stratified into two groups by sex and then randomised using an online tool (“Clinical Trial Randomization Tool.” The National Cancer Institute's Division of Cancer Prevention, <https://ctrandomization.cancer.gov>), resulting in two lists of numbers. The aim is to include an equal number of men and women in each group.

Participants will be assigned to these lists in the order of inclusion and thus randomised accordingly.

### 6.6.3 Blinding and Unblinding

The packaging will be numbered by a researcher. These numbers will then be used for randomisation and correspond to participant numbers.

During the final visit, the participant's treatment will be unblinded by this researcher. Each participant has a separate envelope indicating their treatment, allowing unblinding of an individual participant without revealing the treatment of others.

This researcher does not collect participant data or perform measurements on participant samples. Randomisation, blinding, and unblinding are the only tasks assigned to this researcher.

Unblinding will be documented in the unblinding register.

#### **Emergency Unblinding**

In exceptional circumstances, such as severe adverse events or hospitalisation, the participant's treatment may be unblinded.

The participant can contact a study staff member. The individual envelope for that participant can be opened to reveal the treatment.

Unblinding must always be reported to the principal investigator – medical monitor.

## 6.7 Trial Intervention Compliance

Compliance will be monitored in the "Drug Dispensation & Accountability Log."

At the end of the study, the remaining number of capsules will be counted and subtracted from the number originally provided. This will determine the number of capsules taken. The ratio of capsules actually taken to the expected number will be expressed as a percentage to reflect compliance.

## 6.8 Concomitant Therapy

Participants may not use dietary supplements and/or chronic medication.

Participation is possible if the intake of dietary supplements is stopped at least 10 days before the screening visit and throughout the study duration.

For chronic medication use, an individual assessment will determine whether the medication could affect the study endpoints or whether taking the study product is contraindicated.

For example, participation is possible for individuals using antihypertensive drugs if the dosage is stable and will not change during the study. The participant must still meet the inclusion criterion.

Individuals who have been using, for example, a PPI for several months may also participate.

## **7. Discontinuation of Trial Intervention and Participant Withdrawal from Trial**

### **7.1 Discontinuation of Trial Intervention**

The treatment may be discontinued if the participant or the investigator wishes.

#### **7.1.1 Criteria for Permanent Discontinuation of Trial Intervention**

The treatment will be stopped if the participant meets any exclusion criteria during the study, such as starting smoking or changing their diet.

The treatment may also be stopped if the participant wishes, experiences discomfort from the treatment, or for any other reason.

The participant must return any remaining study product capsules.

#### **7.1.2 Temporary Discontinuation or Interruption of Trial Intervention**

Temporary discontinuation of treatment is not allowed. Stopping the treatment will result in exclusion from the study.

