\* This always refers to the absolute difference compared to the baseline value after 8–9 weeks, unless stated otherwise.

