### **7.3 Lost to Follow-Up**

Due to the short treatment duration, the proportion of participants who do not complete the study is expected to be low. Additional participants will be recruited to ensure sufficient statistical validity. Participants who do not attend the final visit or fail to complete the study will not be replaced.

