## 9. Statistical Considerations

### 9.1 Statistical Analysis

Demographic data and baseline values will be used to describe the study groups.

The difference in each parameter compared to baseline will be analyzed using ANCOVA by treatment group, adjusted for baseline values. An  $\alpha$ -level of 0.025 will be applied for the primary analysis. For secondary and exploratory analyses, an  $\alpha$ -level of 0.05 will be used.

The absolute change from baseline in blood pressure over time will be studied using Linear Mixed Models. Baseline value, treatment group, time point, and the interaction between treatment group and time point will be fixed variables. Participant ID will be a random variable.

As sensitivity or exploratory analyses, predictors such as sex, age, baseline values, or compliance may be added to the models to assess whether they have a significant effect.

Subgroup analyses may also be performed, and other continuous parameters can be studied using the same method.

No interim analysis is planned.

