### 10.3 Data Protection

The identity and participation in this study will be treated with strict confidentiality. The participant will not be identified by name or in any other way in files, results, or publications related to the study. To guarantee privacy, data will be pseudonymized. All further processing will be carried out on these pseudonymized data. The link between the pseudonym and the individual will be retained only to allow certain information to be communicated back to the participant in their own interest.

The participant consents to the use of personal data collected for this study. This consent can be withdrawn at any time. If participation ends prematurely, the original consent allows the use of data collected during the period the participant was actively involved in the study. Only individuals directly involved in the study will have access to personal data. Data will not be shared with third parties. Researchers will retain the data for a period of 25 years.

The participant has the right to ask the researcher which data are collected and for what purpose. The participant may request corrections or deletion of certain data or ask that data no longer be used. All data will be handled in accordance with the “Directive on the protection of individuals regarding the processing of personal data” and applicable national legislation, including the European General Data Protection Regulation (GDPR – EU2016/679) and Belgian law implementing this regulation. Questions regarding data management can be addressed to the study physician or treating physician.

If the participant feels that their rights regarding personal data are not adequately respected, they may contact the Data Protection Officer, who will take appropriate measures. The participant also has the right to file a complaint with the Belgian Data Protection Authority. More information: <https://www.uza.be/privacy.html>.

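### Stopping the capsules means exclusion from the study, so no week 8–9 blood pressure is collected from stoppers and the primary comparison can rest only on those who stayed on product

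*Protocol*

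**What the plan says.** Section 7.1.2 bars temporary interruption and adds "Stopping the treatment will result in exclusion from the study". The sentence stands under the heading on interruption, but its wording covers any stop.

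Section 7.1 lets the participant or the investigator end treatment. Section 7.1.1 gives two further routes: "The treatment will be stopped if the participant meets any exclusion criteria during the study, such as starting smoking or changing their diet" and "The treatment may also be stopped if the participant wishes, experiences discomfort from the treatment, or for any other reason". The only follow-on step there is the return of capsules. Section 7.3 adds "Participants who do not attend the final visit or fail to complete the study will not be replaced".

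On the endpoint, the note to the table in section 3.2 reads "This always refers to the absolute difference compared to the baseline value after 8–9 weeks, unless stated otherwise", and section 8.1.3 places that measurement at the final visit. On the analysis, section 9.1 says "The difference in each parameter compared to baseline will be analyzed using ANCOVA by treatment group, adjusted for baseline values" and also "The absolute change from baseline in blood pressure over time will be studied using Linear Mixed Models". Section 10.3 says that, after early termination, "the original consent allows the use of data collected during the period the participant was actively involved in the study".

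The protocol names no analysis set and no method for missing final values, and it schedules no measurement after a participant has been excluded.

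**The concern.** The rule ties being measured to staying on product. Discomfort may be more frequent on one treatment. Some exclusion criteria could be met because of how blood pressure develops: section 6.8 admits users of antihypertensive drugs only while their dose stays stable, so a dose change after a rise in pressure could lead to removal. That route is a plausible reading; the protocol does not state it. Investigator choice and the open-ended reasons in 7.1.1 leave the filter undefined.

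If people leave for reasons linked to treatment and outcome, those with a week 8–9 value are no longer the randomised groups. The trial then cannot directly estimate the effect of being assigned the extract. The gap arises from a data-collection rule, so the protocol is the place to close it.

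A smaller wording matter belongs with it. Section 7.1.1 gives a change of diet as an example of an exclusion criterion. Section 5.4 does not list it, and section 5.5.1 only asks participants to keep their eating habits.

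**Working it through.** **1. The plan's own figure.** Section 9.2 gives a reduction of 10.4 mmHg, SD 11.4, alpha 0.025 and power 80%. Sidedness is not stated; two-sided is assumed because it reproduces the stated number. For a two-sample t-test the noncentrality is λ = (δ/σ)·√(n/2) with 2n − 2 degrees of freedom.
- n = 25: λ = (10.4/11.4)·√12.5 = 3.23, power 81.6%. n = 24 gives 79.7%.
- One-sided 0.025 would need only 20 per group.
- Dropout: 25/(1 − 0.10) = 27.8, rounded up to 28.

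Both 25 and 28 reproduce. The 10% is a general allowance, so stoppers are part of it.

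**2. What happens to a stopper's primary outcome.** Stop → excluded (7.1.2) → no final visit → no 8–9 week change (3.2, 8.1.3) → nothing observed for the ANCOVA (9.1). Section 10.3 permits use of data already collected. Someone who stops after week 4 therefore has a week-4 value for the mixed model; someone who stops before week 4 has baseline only. Neither has a final value.

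**3. Bias when stoppers differ by a fixed amount (assumptions).** Suppose no true effect of assignment, and stoppers' change g mmHg worse than completers'. With the overall mean at zero, completers in an arm average −p·g, where p is the proportion stopping. The bias of active minus placebo is −(p_active − p_placebo)·g, and a negative value favours active. All three rows average 10% stopping.

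| Stopping, active v placebo | g = 5 | g = 10 | g = 15 | Simulated type I error, g = 10 |
|---|---|---|---|---|
| 10% v 10% | 0 | 0 | 0 | about 2.6% |
| 15% v 5% | −0.5 | −1.0 | −1.5 | about 2.9% |
| 20% v 0% | −1.0 | −2.0 | −3.0 | about 5.5% |

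Reversing the arms reverses the sign.

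**4. Bias when stopping depends on the outcome in one arm (assumptions).** No true effect, 28 per arm, SD 11.4, pooled t-test at two-sided 0.025. The log-odds of leaving are −2.5 + b × (change in SD units), in one arm only.
- b = 0.5: 8.3% leave, bias about 0.5 mmHg, type I error about 2.6%.
- b = 1.0: 10.5% leave, bias about 1.1 mmHg, type I error about 3.3%.
- b = 1.0 in both arms: no bias, about 2.5%.

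Repeated runs move the error rates by about 0.1 percentage point.

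**5. Price of following stoppers.** Assume a proportion p of the active arm stops, keeps none of the 10.4 mmHg, and the SD stays 11.4. The effect is 10.4·(1 − p).

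| p | Effect, mmHg | Power at 28 per group | n per group for 80% |
|---|---|---|---|
| 0% | 10.40 | 86.3% | 25 |
| 5% | 9.88 | 82.3% | 27 |
| 10% | 9.36 | 77.6% | 30 |
| 20% | 8.32 | 66.5% | 37 |

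For comparison, losing 10% and testing about 25 per group against the full 10.4 mmHg gives the 81.6% of step 1.

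**The case against.** Exclusion from the study is not the same as exclusion from the analysis. No analysis set is named, section 10.3 lets earlier data be used, the mixed model can take week-4 values, and an unseen analysis plan may deal with missing outcomes. Section 7.3 also expects few non-completers. Much of this stands: a reader might infer that the protocol prescribes a completers-only analysis, and it does not say so. It does remove the week 8–9 value of every stopper, and no later analysis choice can restore an observation that was never made.

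Two other stronger readings are tempting. One is that attrition from this rule comes on top of the 10% allowance. Section 9.2 budgets dropout in general, so adding stoppers would count them twice. The other is a severe inflation of the type I error. Removing the three largest rises from one arm and none from the other does give about 2.2–2.3 mmHg and about 8%. The protocol contains no such rule, however, and part of the inflation comes from the trimming itself: removing the top three from both arms gives no bias yet still rejects in nearly 5% of trials, because the SD shrinks. The milder cases in step 4 are the fairer guide.

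**Conclusion.** The point holds in a limited form. The protocol stops collecting the primary outcome when a participant stops the product, for post-randomisation reasons that can depend on treatment or outcome. The observed week 8–9 comparison can therefore rest only on those who stayed on product.

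The document fixes neither the size nor the direction of the bias. Under the assumptions of step 4 it is about 0.5–1.1 mmHg, roughly 5–11% of the planned 10.4 mmHg (0.5/10.4 and 1.1/10.4), with type I error of 2.6–3.3% against 2.5%. A marked imbalance such as 20% against 0% would do more; balanced stopping unrelated to outcome does nothing. The calculation of 25 and 28 per group is correct as stated. The case for change is that the missing values cannot be recovered later, while the visits that would supply them are already scheduled.

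**What to change.** Leave the rules on when capsules stop as they are. In 7.1.2, replace the exclusion sentence with wording such as: *Participants who stop the study product are, unless they withdraw consent, still measured at week 4 and week 8–9, and are analysed by ANCOVA in the group to which they were randomised.* Report completers as a sensitivity analysis. The primary model need not change; the mixed model already in 9.1 can serve as a supporting analysis for those with only a week-4 value.

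Three passages need to agree with the new sentence:
- Section 8.6.1 has its own exclusion wording and must be reconciled.
- The diet example in 7.1.1 must be reconciled with the list in 5.4.
- Section 10.3 should make clear that stoppers who continue with visits still count as taking part.

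The cost is a short amendment, a few extra blood pressure visits and a diluted effect. Power at 28 per group is about 86% with no stopping, 82% with 5% and 78% with 10%, if stoppers keep no effect (assumption). The last falls below the planned 80%, and 30 per group would be needed to restore it. The sponsor should state which of these it accepts.

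Section 4.4 places the end of recruitment in February 2024. If the visits are already past, what remains is to report stopping by arm with reasons and timing, and to examine how sensitive the result is to the missing final values.

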### **7.2 Participant Withdrawal for the Trial**

The participant may withdraw from the study at any time, for any reason, and without any consequences.

The participant must return any remaining study products.

### **7.3 Lost to Follow-Up**

Due to the short treatment duration, the proportion of participants who do not complete the study is expected to be low. Additional participants will be recruited to ensure sufficient statistical validity. Participants who do not attend the final visit or fail to complete the study will not be replaced.

## 8. Trial Assessment and Procedures

### 8.1 Visits and Sampling

The study consists of 3 visits: a screening visit, an intermediate blood pressure measurement, and a final visit

#### 8.1.1 Screening visit

Potential candidates are invited for a screening visit. The visit includes the following actions:

- Review the ICF, answer questions, and sign (see 10.2 Informed Consent)
- Complete contact form (see 8.4 Screening Procedures)
- Measure blood pressure 3 times (see protocol “Blood Pressure Measurement”)
- Check inclusion and exclusion criteria using the inclusion checklist (see 8.4 Screening Procedures)
- Complete Food Frequency Questionnaire (FFQ)
- Complete baseline questionnaire (see 8.4 Screening Procedures)
- Measure weight, height, and waist circumference (see 8.4 Screening Procedures)
- Blood sampling by a nurse (34 mL) (see protocol “Blood Sampling”)
  - o 2x Serum tube (2 × 7 mL)
  - o 3x EDTA tube (3 × 4 mL)
  - o 1x Glucose tube (1 × 4 mL)
  - o 1x Homocysteine tube (1 × 4 mL)

